**Figure 3 figure3:**
[figure not shown]
*MyCoach* architecture. JHU: Johns Hopkins University.

Both interventions (B) and (C) have personalized and tailoring components. Each participant completes a questionnaire about personal family status, habits, pet ownership, work status, and preferred schedule to wake up, eat, work, and relax. All of this information, plus the individual physical performance data, are used to personalize and tailor each individual experience with both interventions. All participants are motivated to increase their physical activities to at least 10,000 steps per day regardless of the arm assignment. Participants in all arms are able to keep the Fitbit Charge 2 HR as a gift from the study team at the end of the trial.

The study team designed each intervention for a specific population, cancer survivors, to best fit their needs, thus the current intervention design is only suitable for such a target population. However, the innovative study design, operations, and technology development make this study easily adaptable for the more general population with slight design modification(s).

### Blinding

Due to the nature of the study interventions, study participants are not blinded. Data for the principal outcomes, however, are collected using sensors. Therefore, the study data analyst is blinded during data collection and during analysis.

### Study Outcomes

The aim of this study is to assess the effectiveness of different technological approaches in increasing physical activity among overweight and/or obese cancer survivors captured by wearable sensors (Fitbit Charge 2 HR). The primary outcome is the percent change in daily steps from the 1-week run-in to the end of the 4-week intervention period. The data for the primary aim is collected in real-time and transferred simultaneously to the computational server of the Johns Hopkins University via an application programming interface (API) that directly transmits the data from the user’s wearable device to the server. Participant wear-time is validated using the heart rate sensor readings on a minute-by-minute basis.

In addition to the primary outcome, the study will examine the following secondary outcomes: 1) total number and duration of activity bouts (defined as 3 minutes or more of uninterrupted activity); 2) fragmentation indices (counting transitions between active/inactive periods) and variability indices (counting the magnitude of transitions between different levels of physical activity); 3) daily diurnal patterns of activity that model patterns in minute-by-minute profiles; and 4) weekly and daily trends of total steps. Levels of physical activity intensity will be defined using each participant’s personalized heart rate reserve.

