### Statistical Analyses

As the primary outcome variable is the 4-week change from the baseline in the average number of steps per day, the primary analysis will use a two-sample t-test to compare each active intervention arm with the control arm based on intent-to-treat strategy. A Bonferroni correction will be used to adjust for multiple comparisons.

For the secondary outcomes (activities bouts, fragmentation, and patterns), a linear regression model will be fitted for the 4-week change from the baseline in the number of steps and duration of activity bouts each day. The independent variables include the baseline number of steps, study arm (modeled by two dummy variables for the two active treatment arms, and the control arm is treated as reference group), and any potential baseline confounding factors. Poisson regression will be used to analyze the total number of activity bouts, fragmentation indices, and variability indices. The independent variables include baseline number of steps, study arm, and any potential baseline confounding factors as the independent variables. In all analyses, data will be properly transformed to fit the model assumption before regression analysis. Although missing data is not anticipated to be a challenge, small amount of non-wear time for charging, bathing, etc. will have minimal effects on the primary study aim since it depends on the average steps across the intervention period. Since Stratified Permuted Block Randomization is being employed, we will consider minimization to balance interventions simultaneously over several prognostic factors to ensure equal distribution across arms. To date nearly 80% of the target population has been enrolled, and only one participant stopped wearing the tracker one day a week for religious reasons.

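### The fragmentation endpoint is an unnormalised count of active/inactive transitions, so an arm difference in it mixes how much participants move with how broken up their activity is

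*Protocol article*

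**What the plan says.** The Study Outcomes section of the protocol article has four groups of secondary outcomes. The first is "total number and duration of activity bouts (defined as 3 minutes or more of uninterrupted activity". The second is "fragmentation indices (counting transitions between active/inactive periods) and variability indices (counting the magnitude of transitions between different levels of physical activity". No denominator is given for either index, such as active time, inactive time or wear time.

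The Statistical Analyses section treats them as counts: "Poisson regression will be used to analyze the total number of activity bouts, fragmentation indices, and variability indices". On covariates it says "The independent variables include baseline number of steps, study arm, and any potential baseline confounding factors as the independent variables". It names no offset and nothing measured after baseline. The only other relevant sentence is general: "In all analyses, data will be properly transformed to fit the model assumption before regression analysis".

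Neither section says whether a higher or a lower value of either index is favourable.

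The Intervention section gives the aim: "All participants are motivated to increase their physical activities to at least 10,000 steps per day regardless of the arm assignment". The sample Coachtext message there suggests a stroll of at least ten minutes.

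**The concern.** Fragmentation is meant to describe how broken up a given amount of activity is. A raw count of transitions does not hold the amount fixed. Each separate active spell contributes one transition in and one out, so the count is twice the number of spells. It can grow because activity is chopped into shorter pieces, or because there is more of it.

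In this trial the second route is the intended effect of treatment. If Coachtext or MyCoach gets participants to take extra walks, the transition count in that arm can rise although typical spells are unchanged or longer. Baseline steps in the model adjust for where participants started. They do not adjust for a change in volume that occurs during the intervention and is caused by it.

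What is at stake is the reading of a secondary result: a difference in the count could be reported as a change in activity pattern when it reflects volume, and its sign could be opposite to the change in continuity.

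**Working it through.** The documents give no figure for these endpoints, so there is none to reproduce. The check is of how the count behaves. **All activity values below are assumptions**; the documents give no active minutes or spell lengths. Here an active minute means any minute the tracker classes as active, not questionnaire-reported exercise.

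**Formulas.** For *N* active spells totalling *A* active minutes:
- transitions = 2*N* = 2*A* / mean spell length
- active-to-inactive probability = *N* / *A* = 1 / mean spell length

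**Same extra volume, added in three ways.** Assume 100 active minutes in 40 spells (mean 2.5 min) and add 20 minutes.

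| Pattern | Active min | Spells | Transitions | Active-to-inactive probability |
|---|---|---|---|---|
| Start | 100 | 40 | 2×40 = 80 | 40/100 = 0.40 |
| Two separate 10-min walks | 120 | 42 | 84 (+5%) | 42/120 = 0.35 |
| Eight more 2.5-min spells | 120 | 48 | 96 (+20%) | 48/120 = 0.40 |
| Existing spells lengthen to 3.0 min | 120 | 40 | 80 (0%) | 40/120 = 0.33 |

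The two 10-minute walks are the row closest to the sample coaching message. There the count goes up while activity becomes less broken up. The +20% row is an unfavourable case: it supposes that all the added walking comes in short fragments.

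**When the signs disagree.** Add one separate spell of length *L*. The count goes from 2*N* to 2*N* + 2, so it always rises. The probability goes from *N*/*A* to (*N*+1)/(*A*+*L*), which is lower when *A*(*N*+1) < *N*(*A*+*L*), that is, when *L* > *A*/*N*. So the signs are opposite whenever the added spell is longer than the current mean spell. This condition does not depend on the assumed starting values; the size of the shift does.

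**Second check with a different assumed pattern.** Take 960 waking minutes with alternating active and inactive spells of mean length *a* and *i*. Transitions per day = 2×960/(*a*+*i*); active minutes = 960×*a*/(*a*+*i*).

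| *a*, *i* (min) | Active min | Transitions | Transitions per active hour |
|---|---|---|---|
| 4, 28 (start) | 120 | 60.0 | 30.0 |
| 4, 18.667 (more spells, same length) | 169.4 | 84.7 (+41%) | 30.0 |
| 5.6, 26.4 (longer spells) | 168.0 | 60.0 (0%) | 21.4 |
| 8, 33.14 (fewer, longer spells) | 186.7 | 46.7 (−22%) | 15.0 |

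A minute-level simulation of 4,000 days per pattern gave 60.0, 84.8, 60.2 and 46.7 transitions, in agreement. Activity rises in every row after the first, yet the count rises, stays flat or falls. The index per active hour stays at 30.0 when only volume changes and falls when spells lengthen.

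**The case against.** **The article is a condensation.** The parentheses may be short glosses, the outcomes are called indices, and a denominator or offset could sit in a fuller document. Wear time is validated minute by minute, and a Poisson model can carry an offset. This lowers confidence but does not remove the point. The article states a definition by counting, a count model to match and a covariate list, and the three agree with one another. The transformation sentence concerns model fit, not normalising for volume.

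**Other outcomes help.** Bout number and duration, diurnal profiles and step trends are also secondary outcomes. A careful reader could set a higher transition count beside longer bouts and see what happened. That stands, and it is why the claim is only that the count cannot be interpreted by itself.

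**Stronger readings that the documents do not support:**
- *The count rises whenever participants walk more.* It does not: lengthened or merged spells leave it flat or lower it.
- *The plan scores an effective arm as worse.* No favourable direction, hypothesis or success rule is stated for either index. The risk lies in interpretation.
- *The count merely repeats the bout outcome.* Bouts need at least 3 minutes. With a constant stopping chance of 0.40 per active minute, only 0.6² = 36% of spells last that long, so most transitions would come from spells that are not bouts.
- *Variability has the same fault.* The wording does not say whether magnitudes are summed, averaged or tabulated. Only a sum would carry the volume problem in the same way.

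**Conclusion.** The point holds for fragmentation. As stated, the endpoint is a transition count that combines amount and continuity of activity, and the stated covariates do not separate them. When added walking comes as separate spells longer than the current mean, the count and the chance of stopping per active minute move in opposite directions.

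The size depends on assumed patterns. In the case closest to the trial's own coaching message, the count moves by +5% while the active-to-inactive probability falls from 0.40 to 0.35, which is −12.5%. Larger shifts are possible, but only under less favourable assumptions about how walking is added.

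For variability the conclusion is limited to an ambiguity to be resolved. These are secondary outcomes in a 42-person pilot, and the primary step comparison is untouched. The change is worth making before the analysis because it costs little.

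**What to change.** 1. Define fragmentation as active-to-inactive transitions divided by active minutes. Alternatively, keep the Poisson model for those transitions and add log active minutes as an offset.
2. Report the inactive-to-active rate separately, per inactive wear minute.
3. State the direction: a lower active-to-inactive rate means less fragmented activity.
4. Keep raw transition counts as descriptive only.
5. For variability, say how magnitudes are combined. If they are summed, use the mean magnitude per transition instead, with a model suited to a continuous outcome.

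The cost is a change of wording in the outcome definitions and the analysis section. The same minute-level tracker and wear-time data serve, with no new collection. The small downside is that the endpoints become a rate or a mean, so the regression for each must be named to match.

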### Privacy and Safety Aspects

The Johns Hopkins School of Medicine IRB reviewed the protocol, information technology (IT) solutions, safety, and security of the data collection & storage, and approved the study (# IRB00113882). The Sidney Kimmel Comprehensive Cancer Center at Johns Hopkins (SKCCC)/The Clinical Research Review Committee (CRC) also reviewed the protocol and found that this study poses minimal risk to the participants, and assigned Minimum Risk category to this study. SKCCC/CRC recommended forming Data and Safety Monitoring Board for this study & SKCCC/CRC will conduct random audits. To ensure the safety and security of participant information, the *Coachtext* and *MyCoach* were programmed on the Johns Hopkins University server, avoiding the use of commercial servers by Amazon Inc. for public developers. Although the commercial-use free Amazon Web Services server is available with Alexa, it is not compliant with the institutional requirements. However, the study team connected Amazon Echo and Alexa’s voice to the server behind the Johns Hopkins University firewall to protect the user’s privacy. The study also provided a Privacy Policy Statement for the *MyCoach* for the participant who will enable the skills on their Echo devices. This statement explains how data will be shared, stored and processed by Johns Hopkins. The written consent form and the electronic sign-in for each study arm also provide clear descriptions of what data will be collected from each individual and the manner in which it will be used. The study team will assure participants that all automated data collection processes will be stopped after the participant finishes the program or if he/she decides to withdraw from the study. To add another layer of security, *MyCoach* is enabled only for the study participants and not open for public users. Data from the wearable sensors are prescheduled to transfer to our secure server only during the study period. Following the end of the study, the transfer is halted automatically. Regardless of study arm assignment, and in addition to written consent, all users need to complete an online data transfer agreement using their wearable sensor credentials.

### Statistical Analyses

As the primary outcome variable is the 4-week change from the baseline in the average number of steps per day, the primary analysis will use a two-sample t-test to compare each active intervention arm with the control arm based on intent-to-treat strategy. A Bonferroni correction will be used to adjust for multiple comparisons.

For the secondary outcomes (activities bouts, fragmentation, and patterns), a linear regression model will be fitted for the 4-week change from the baseline in the number of steps and duration of activity bouts each day. The independent variables include the baseline number of steps, study arm (modeled by two dummy variables for the two active treatment arms, and the control arm is treated as reference group), and any potential baseline confounding factors. Poisson regression will be used to analyze the total number of activity bouts, fragmentation indices, and variability indices. The independent variables include baseline number of steps, study arm, and any potential baseline confounding factors as the independent variables. In all analyses, data will be properly transformed to fit the model assumption before regression analysis. Although missing data is not anticipated to be a challenge, small amount of non-wear time for charging, bathing, etc. will have minimal effects on the primary study aim since it depends on the average steps across the intervention period. Since Stratified Permuted Block Randomization is being employed, we will consider minimization to balance interventions simultaneously over several prognostic factors to ensure equal distribution across arms. To date nearly 80% of the target population has been enrolled, and only one participant stopped wearing the tracker one day a week for religious reasons.

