
## Methods

### Design

This is a three-arm single center pilot randomized trial with allocation ratio of 1:1:1. The arms are: (A) control, in which participants are provided with written materials about the benefits of physical activity; (B) text-messaging intervention, where participants receive multiple motivational messages from an automated, data-driven algorithmic text message program via mobile phone (*Coachtext*); and (C) voice-assist intervention, in which participants are provided with an in-home autonomous Intelligent Agent using data driven Interactive Digital Voice Assist on the Amazon Alexa/Echo (*MyCoach*).The trial duration is 5 weeks – a one-week run-in phase to establish baseline physical activity, followed by 4 weeks of intervention (Figure 1). Physical activity outcomes are captured via wearable sensors (Fitbit Charge 2 HR). Table 1 includes a schedule of enrollment, interventions, and assessments.

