### Sample Size

The investigators designed this study to compare: (i) a dialogue Intelligent Agent, using data driven Interactive Digital Voice Assist on Amazon Alexa/Echo speaker (*MyCoach*) in assisting participants in increasing their physical activity, with (ii) a text messaging intervention and (iii) a written information/self-motivation intervention. To detect at least a 2000 step difference in means at a SD of 1800 steps/day (the standard deviation of the 28-day daily sample mean is 1800 steps), with a 2-sided alpha of 0.05, and power of 0.8, or 80, 13 participants are required per arm (39 participants total (with Bonferroni correction of 2 comparisons)). To account for intention to treat and possibly per-protocol analysis, the study team subsequently added an additional participant to each arm; therefore, 14 participants are being recruited per arm, for a total of 42 participants. Also, to account for dropout, the protocol also allows the addition of patients to replace those who dropout due to a condition/illness that prevents them from participating in the trial during the run-in period.

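### Optional, low-cost improvement: Holm on the same two t-tests keeps the family-wise error at 0.05 and never rejects less than the planned Bonferroni correction

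*Protocol article*

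**What the plan says.** Under Statistical Analyses, the protocol article states that "the primary analysis will use a two-sample t-test to compare each active intervention arm with the control arm" by intention to treat, and then that "A Bonferroni correction will be used to adjust for multiple comparisons". The Sample Size section uses the same correction for the same number of tests: "13 participants are required per arm (39 participants total (with Bonferroni correction of 2 comparisons"). The design figures there are "To detect at least a 2000 step difference in means at a SD of 1800 steps/day", "with a 2-sided alpha of 0.05, and power of 0.8". One participant per arm was then added, so that "14 participants are being recruited per arm, for a total of 42 participants".

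With two comparisons, Bonferroni holds each test at two-sided 0.05 / 2 = 0.025, whatever the other test shows. The article does not mention a stepwise procedure and says nothing that conflicts with Bonferroni.

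**The concern.** For two hypotheses, Bonferroni leaves something unused. Once one comparison is significant at 0.025, the other can be tested at 0.05 without exceeding a family-wise error of 0.05. This is the Holm procedure. It rejects everything Bonferroni rejects and sometimes one hypothesis more, under the same assumptions.

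At stake is the second of two effective interventions. Both technologies are candidates against the same control, the arms are small, and recruitment is nearly finished (Trial Status: 39 enrolled as of January 2018). Power that needs no further participants is therefore worth considering, provided its limits are stated.

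**Working it through.** **Inputs.** From Sample Size: difference 2000 steps/day, SD 1800, two-sided alpha 0.05, power 80%, two comparisons, 13 per arm raised to 14. From Design: allocation 1:1:1. From Statistical Analyses: two-sample t-tests against a shared control.

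**Assumption.** The article defines 1800 as the SD of the 28-day mean of daily steps, while the tested variable is a change from baseline. I apply 1800 to the change and vary it in step 6. Data are taken as normal and complete.

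**1. The plan's own figure.** Per-arm n = 2 (z₁₋α/₂ + z₀.₈₀)² (SD/difference)², with (1800/2000)² = 0.81.
- At alpha 0.05: 1.62 × (1.960 + 0.842)² = 12.7, so 13 (14 by the exact t-test).
- At alpha 0.025: 1.62 × (2.241 + 0.842)² = 15.4, so 16 (17 by the exact t-test).

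The stated 13 therefore matches the uncorrected level, not the Bonferroni level. That is a separate point about the sizing, but it explains why power at 14 per arm is below 80% under the planned test.

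**2. Power of one Bonferroni test at 14 per arm.** Noncentrality = (2000/1800) × √(14/2) = 2.940, with 26 degrees of freedom. At two-sided 0.025 the critical value is 2.379 and power is 71.1%. At two-sided 0.05 the critical value is 2.056 and power is 80.8%. Holm must lie between these two values. It approaches the upper one only if the other comparison is almost certain to be significant.

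**3. Error control of Holm.** If both nulls are true, an error requires the smaller p-value to be at most 0.025, which has probability at most 2 × 0.025 = 0.05. If one null is true, an error requires that comparison's p-value to be at most 0.05. Family-wise error is thus at most 0.05 in every case.

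**4. Simulation.** 400,000 three-arm trials per scenario, 14 per arm, SD 1800, shared control, pairwise t-tests. Each cell shows Bonferroni / Holm.

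| True effects (steps) | First arm | Second arm | At least one | Both |
|---|---|---|---|---|
| 2000 and 2000 | 71.0% / 76.7% | 71.3% / 76.9% | 85.1% / 85.1% | 57.1% / 68.5% |
| 2000 and 1000 | 71.1% / 71.9% | 19.9% / 27.9% | 72.7% / 72.7% | 18.3% / 27.0% |
| 2000 and 0 | 71.1% / 71.2% | 2.5% / 4.1% | 72.0% / 72.0% | 1.6% / 3.4% |
| 0 and 0 | 2.5% / 2.7% | 2.5% / 2.7% | 4.7% / 4.7% | 0.4% / 0.8% |

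A repeat run with a different seed gave 56.8% / 68.4% for detecting both in the first row. The At least one column must be identical, because either rule needs the smaller p-value to be at most 0.025.

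**5. Where Holm differs.** Holm adds a rejection only when one p-value is at most 0.025 and the other lies between 0.025 and 0.05. With both effects at 2000 this happens in 68.5% − 57.1% = 11.4% of trials. Each such trial adds one rejection, shared equally between two equivalent arms, so the gain per comparison is 11.4 / 2 = 5.7 points, which agrees with the table. A 97.5% interval excludes zero only if p is below 0.025. In every one of these trials the Bonferroni interval for the added rejection therefore includes zero.

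**6. Range for the SD.** Same simulation, both effects 2000, Bonferroni / Holm:
- SD 1400: about 91% / 94% per comparison; 85% / 91% for both.
- SD 2200: about 52% / 58% per comparison; 35% / 47% for both.

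The gain has the same direction throughout and is 3 to 6 points per comparison.

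**The case against.** The strongest case for leaving the plan alone is that nothing in it is wrong. Bonferroni is specified in advance, controls the family-wise error, and is named consistently in the sizing and the analysis. It also has a practical merit: the test and the simultaneous interval always agree. The article calls the study a pilot of a preliminary effect, so intervals may matter as much as the tests. All of this stands, and it is why the change is optional.

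A reader might infer three stronger things, none of which the article supports.
- **That the correction is an error or a contradiction.** It is neither; Sample Size and Statistical Analyses agree on it.
- **That Bonferroni always costs power here.** It costs nothing in the chance of finding at least one effective arm, and about 0.1 point when only one arm works. In that last case Holm's extra rejections fall almost entirely on the ineffective arm (2.5% to 4.1%, still within 5%).
- **That Holm repairs the gap to 80%.** At SD 1800 it gives 71% to 77% per comparison in the scenarios examined. The gap comes from the sizing, where 16 to 17 per arm would be needed under the correction the article names.

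Step-down Dunnett is also tempting because it uses the correlation created by the shared control. Its standard form pools the variance over three arms, so it would replace the pairwise t-test that the article fixes. Offering it as an alternative would also leave the primary method open.

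**Conclusion.** The point holds as an inexpensive improvement, not as the correction of a mistake. With 14 per arm, SD 1800 for the tested change, normal data and no missing values, Holm adds about 6 points of power per comparison and about 11 points for detecting both, if both interventions reach 2000 steps. It adds about 8 points for the weaker arm if the effects are 2000 and 1000. The size depends on the SD assumption, which the article does not settle. That Holm never rejects less, with the same error guarantee, does not depend on it. The price is a visible mismatch between test and interval in exactly those trials where Holm helps.

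**What to change.** Before unblinding, replace the Bonferroni sentence under Statistical Analyses with: *The two comparisons with control will be tested by the Holm procedure at family-wise two-sided alpha 0.05.* Name Holm alone, keep the two-sample t-tests as they are, and date the amendment. The Randomization and Blinding sections describe a blinded analyst, so a change made at that stage would be credible.

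Add one sentence on reporting: the Holm test decides significance, and the Bonferroni 97.5% simultaneous intervals are shown as conservative and may include zero for a comparison that Holm declares significant.

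The cost is two sentences and no participants. If the sponsor values agreement between test and interval more than the added power, keeping Bonferroni is defensible. The sample-size statement needs its own correction either way.

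### The Poisson models for total bouts and transition counts list no exposure term, so any arm difference in days observed would pass straight into the rate ratio

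*Protocol article*

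**What the plan says.** All references are to the protocol article.

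- **Model and outcomes** (Statistical Analyses): "Poisson regression will be used to analyze the total number of activity bouts, fragmentation indices, and variability indices".
- **Terms** (same section): "The independent variables include baseline number of steps, study arm, and any potential baseline confounding factors as the independent variables".
- **Outcome definitions** (Study Outcomes): "total number and duration of activity bouts (defined as 3 minutes or more of uninterrupted activity" and "fragmentation indices (counting transitions between active/inactive periods". Both are worded as quantities that accumulate; neither is given per day or per hour worn.
- **Planned follow-up** (Design): "a one-week run-in phase to establish baseline physical activity, followed by 4 weeks of intervention", the same for every participant.
- **Withdrawal** (Privacy and Safety Aspects): "all automated data collection processes will be stopped after the participant finishes the program or if he/she decides to withdraw from the study".
- **Replacement** (Sample Size): described only for people who drop out during the run-in because of illness.
- **Non-wear** (Statistical Analyses): it is expected to have "minimal effects on the primary study aim since it depends on the average steps across the intervention period". The known case is that "only one participant stopped wearing the tracker one day a week for religious reasons".
- **Wear time** (Study Outcomes): checked minute by minute from the heart-rate sensor.

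Elsewhere in Statistical Analyses, the primary outcome is a mean per day, and the linear secondary model takes steps and bout duration on a daily scale. Only the Poisson outcomes lack a stated time base.

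**The concern.** A total grows with the time over which it is counted. A participant who withdraws halfway through the intervention contributes about half the bouts of an equally active completer, and the listed model has no term to recognise this. The arm coefficient then mixes activity level with length of observation. If withdrawal or worn days differ between arms, part of that difference would be reported as an effect on bouts or fragmentation.

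The plan considers missing wear and dismisses it because the primary outcome is an average. That argument is sound for an average but does not cover the totals.

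**Working it through.** The plan gives no figure for these models, so there is nothing to reproduce.

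**Inputs from the article:** 14 participants per arm; 28 intervention days; terms as listed above.
**Assumed, not in the article:** 1 to 3 of 14 stop early in one arm, everyone else is observed for 28 days, and true daily rates are equal. The simulations also assume 10 bouts per day.

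**Step 1: what the model estimates.** In a log-linear Poisson model with an arm term and no offset, the fitted ratio is the ratio of arm mean counts. With a common daily rate λ it is

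(λ × mean days, arm 1) / (λ × mean days, arm 2) = mean days, arm 1 / mean days, arm 2.

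λ cancels, so the bias depends on neither the bout rate nor the dispersion. Baseline covariates do not record days observed after baseline.

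**Step 2: numbers.** With k of 14 stopping at day d, mean days = [28(14 − k) + dk] / 14, to be divided by 28.

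| Stoppers in one arm | Day 7 | Day 14 | Day 21 |
|---|---|---|---|
| 1 | 26.5/28 = 0.946 | 27/28 = 0.964 | 27.5/28 = 0.982 |
| 2 | 25/28 = 0.893 | 26/28 = 0.929 | 27/28 = 0.964 |
| 3 | 23.5/28 = 0.839 | 25/28 = 0.893 | 26.5/28 = 0.946 |

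If the stoppers are in the control arm, the day-14 ratios invert to 28/27 = 1.04, 28/26 = 1.08 and 28/25 = 1.12.

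**Step 3: the one documented case.** One day a week off leaves 24 of 28 days, so that person's total falls by 1 − 24/28 = 14%. The arm ratio is (13 × 28 + 24)/(14 × 28) = 388/392 = 0.990.

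**Step 4: effect on the test.** Null simulation, 1,000 runs per setting, two-sided 0.05, stoppers at day 14 in one arm.

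*Counts truly Poisson, no offset:* plain standard errors reject in 35%, 91% and over 99% of runs for 1, 2 and 3 stoppers. With a Pearson (quasi-Poisson) scale the figures are about 1%, 5% and 19%, and the bias in the ratio is unchanged. With a log(days) offset the ratio returns to about 1.00 and rejection is about 5% with either standard error.

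*Between-person variation added (gamma variance 0.1, assumed):*

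| Stoppers | Plain, no offset | Plain, offset | Scaled, no offset | Scaled, offset |
|---|---|---|---|---|
| 0 | 73.6% | 73.6% | 5.4% | 5.4% |
| 2 | 79.1% | 72.0% | 6.3% | 6.1% |
| 3 | 80.7% | 69.1% | 9.5% | 5.7% |

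The offset corrects the estimate. Only the scaled error brings the rejection rate near 5%, and plain Poisson errors fail even with no stoppers.

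**Step 5: which exposure measure.** Suppose three completers in one arm take the device off for 8 hours each night and are otherwise equally active. With 24-hour wear minutes as the offset, arm exposure is (11 × 24 + 3 × 16)/(14 × 24) = 312/336, and the false ratio is 336/312 = 1.077. That matches the effect of two day-14 stoppers in the control arm. Raw wear minutes can therefore create the bias they are meant to remove.

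**The case against.** The strongest reply is that the article does not fix the flaw. It gives no period for the totals, so a total per day is a possible reading. Its list of terms is introduced as what the model includes, which need not be exhaustive. An offset is not usually counted among independent variables, and an analysis plan that is not shown could contain one. Follow-up is also the same length for everyone, and no withdrawal during the intervention is reported.

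Part of this stands. The text does not rule out an offset, and the harm depends on events that the article does not report. But a per-day definition is not stated for these outcomes, although it is for the primary outcome and the linear models. An analysis plan that followed the wording as printed would carry the problem. The general promise to transform data to fit the model does not adjust for exposure.

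A reader might infer that uneven stopping is already distorting the results, or that false-positive rates of 10% or more are to be expected. The documents support neither. With scaled errors and an assumed between-person coefficient of variation of 30%, a separate simulation of 20,000 runs rejected in 5.0% with one control stopping at day 14 and 6.8% with two. It reached 9.9% only with three controls stopping (days 7, 14 and 21) and nobody stopping in the other arm; at a coefficient of variation of 15% that pattern gave 13.0%.

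**Conclusion.** The point holds as a gap in how secondary outcomes are specified. As written, total bouts and transition counts are modelled without an exposure term, and the plan's argument about non-wear does not cover them. Any arm difference in mean observed days passes one for one into the rate ratio: about 0.96, 0.93 or 0.89 for 1, 2 or 3 one-sided stoppers at day 14. That size rests on assumed numbers of stoppers but on no assumption about bout rate or dispersion. The test error rates in the working depend on both.

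It is not a demonstrated bias. The only case on record shifts an arm mean by about 1%, and the primary outcome is unaffected by this point. It is worth correcting because the correction is cheap and each one-sided day-14 stopper removes 14/392 = 3.6% of an arm's observed time.

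**What to change.** 1. Define total bouts and transition counts per valid day, or keep the totals and add log(number of valid days) as an offset. Set the valid-day rule in advance as a waking-hours wear criterion based on the heart-rate data.
2. Use quasi-Poisson or negative binomial standard errors. Without this step the offset does not give a valid test.
3. Do not use raw 24-hour wear minutes as the offset, because differences in night wear would enter the ratio.
4. State for each fragmentation and variability index whether it is a count or a rate, and use no offset for one already defined as a rate.
5. Report valid days by arm, so that any imbalance is visible.

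The cost is a small amount of analysis work and the choice of a valid-day threshold; no new data are needed. If everyone completes with similar valid days, the estimated ratios will hardly change. The offset equalises observation time only. It does not address the possibility that people who stop early would have been less active afterwards.
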